#### Missing data

We will conduct a missing value analysis to identify the patterns in missing variables, before determining whether the baseline characteristics differ between participants with and without missing data in terms of the response variables at the final measurement (6 months). Based on these analyses, we will infer whether missing values are likely to be missing at random (MAR), missing completely at random (MCAR), or missing not at random (MNAR). In the event of MCAR or MAR data, we will use multiple imputation techniques and present the outcome of analyses with and without the imputed data. In the event of MNAR data, we will not replace missing values and we will conduct case analysis when available.

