### Outcome measures

The effectiveness of the program will be assessed based on the following primary and secondary outcomes. The primary outcome will be the caregiver-related quality of life after 3 months. The secondary outcomes will be subdivided to those in the caregiver groups and those in the dementia groups. In the caregiver groups, we will assess quality of life, caregiver burden, experienced health, care utilization, psychotropic medication use, depressive and anxiety symptoms, and perseverance time. In the dementia groups, we will assess the courses of neuropsychiatric symptoms, activities of daily living, utilization of care, costs of care, quality of life, agitation, psychotropic medication use, and dementia severity. Secondary outcome variables will be measured at baseline and after 3 and 6 months and compared between the intervention and control groups.

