#### Outcome analysis

For the primary outcome, the change in the CarerQol-7D score from baseline to 3 months, a linear regression model will be developed to test the response variable for differences between the intervention and control groups, adjusting for the baseline outcome scores. We will perform a primary intention-to-treat analysis for the primary equation, which will be complemented with a secondary per-protocol analysis. The intention-to-treat population will include all information from participants randomized to each treatment arm, whereas the per-protocol population will only include information about those who completed the program to which they were allocated.

For the secondary outcome variables, multilevel analyses will be used to account for the dependency of the repeated measurements. A restricted, iterative, generalized least-squares algorithm will be used to estimate the regression coefficients, while the Wald test will be used to obtain *P* values for each regression coefficient. Linear or binary multilevel analysis will be conducted depending on the outcome measure. Subgroup analyses will be performed to assess the heterogeneity of treatment effects.

Assumptions of the normality and homogeneity of variance in the linear regression models will be assessed by inspecting normal probability plots and plots of standardized residuals compared with predicted values. If assumptions are not met, variables will be transformed to comply with the assumptions. If this does not yield acceptable distributions, variables will be dichotomized or we will use non-parametric statistical analyses. All statistical tests will be two-sided and will be required to meet the 5% significance criterion.

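### The missing-data rule chooses the analysis by inferring MCAR, MAR or MNAR from observed data, answers MNAR with unimputed available cases, and ties its baseline check to 6 months although the primary outcome is at 3 months

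*Protocol article*

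**What the plan says.** The Missing data section of the protocol article sets out a sequence. First comes a missing-value analysis of the patterns. Next comes "determining whether the baseline characteristics differ between participants with and without missing data in terms of the response variables at the final measurement (6 months". Then the mechanism is named, with MNAR as the third option: "Based on these analyses, we will infer whether missing values are likely to be missing at random (MAR), missing completely at random (MCAR), or missing".

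The label decides what follows:

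- MCAR or MAR: "In the event of MCAR or MAR data, we will use multiple imputation techniques and present the outcome of analyses with and without the imputed" values.
- MNAR: "In the event of MNAR data, we will not replace missing values and we will conduct case analysis when available".

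Elsewhere the article fixes the endpoint: "The primary outcome will be the caregiver-related quality of life after 3 months" (Outcome measures). Under Outcome analysis, the primary model is a linear regression of the change in CarerQol-7D from baseline to 3 months, adjusted for the baseline score, with an intention-to-treat primary analysis. Sample size calculation anticipates 10% attrition among 144 dyads.

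**The concern.** Three features of the stated rule do not work.

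1. **The diagnostic cannot deliver the label.** MAR and MNAR differ in whether, given everything observed, missingness still depends on the scores nobody saw. Patterns and baseline comparisons are both observed data. They can argue against MCAR but cannot tell MAR from MNAR.
2. **The MNAR branch does not address MNAR.** Having concluded that missingness depends on unseen scores, the plan fits the model to the seen scores without adjustment, and that branch contains no sensitivity analysis.
3. **The time point does not match.** The baseline comparison concerns responses at 6 months, but the primary outcome is at 3 months. A dyad seen at 3 months and lost by 6 counts as missing in the check, although its primary outcome is complete.

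At stake is the handling of the primary outcome if loss is selective. That is plausible here, because one arm attends a five-day residential programme and the other receives usual care. Selective loss could go uncorrected and unexplored, and the analysis would have been chosen after the data were seen.

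**Working it through.** **Inputs from the documents.** 144 dyads in two equal arms, effect size 0.5, significance 0.05, power 0.8, attrition 10% (Sample size calculation); two-sided tests and baseline-adjusted regression (Outcome analysis).

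**The plan's own figure.** The t-based requirement for 0.5 SD is 64 per arm. 64 / 0.9 = 71.1, rounded up to 72 per arm, which gives 144. The sample size reproduces and this point does not affect it. Expected loss is 0.10 × 144 = 14.4 dyads, leaving 129.6, or 64.8 per arm.

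**Can the baseline comparison identify the mechanism?** This was simulated with 4,000 trials per case. Assumed, not from the documents: baseline–outcome correlation 0.5, true effect 0.5 SD, and a 5% t-test of the baseline score between those with and without an outcome. The estimate is the baseline-adjusted regression on available cases.

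| Mechanism | Missing | Baseline difference flagged | Mean estimate |
|---|---|---|---|
| (a) MCAR | 10.0% | 6% | 0.50 |
| (b) MAR, depends on baseline | 10.5% | 97% | 0.50 |
| (c) MNAR, intervention-arm loss depends on the unseen residual | 10.8% | 5% | 0.65 |
| (d) MNAR, depends on the outcome itself | 11.1% | 48% | 0.47 |

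In (c) the log-odds of loss in the intervention arm rise by 1.2 for each SD that the residual is lower. Control-arm loss is constant at 1 / (1 + e^3) = 4.7%, so intervention-arm loss is 2 × 10.8% − 4.7% = 16.9%.

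Cases (a) and (c) look the same to the check (6% and 5%, both close to the nominal 5%), yet (c) is biased by 0.65 − 0.50 = 0.15 SD. Case (d), when flagged, looks like MAR. No result of the check points to MNAR.

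**When is the available-case regression unbiased?** When missingness depends only on variables in the model, here arm and baseline score. Case (b) shows this: estimate 0.50. Cases (c) and (d) break the condition and the estimate moves. An MNAR judgement says precisely that the condition fails.

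**Size in a milder setting.** Let those lost score δ SD worse than arm and baseline predict, with loss proportions p_I and p_C. The available-case contrast is then off by δ × (p_I − p_C). With average loss at 10% and δ assumed to be 0.5:

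- 10% and 10%: 0.5 × 0 = 0
- 15% and 5%: 0.5 × 0.10 = 0.05 SD
- 20% and 0%: 0.5 × 0.20 = 0.10 SD

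For scale, the standard error with 64.8 per arm and correlation 0.5 is √(2/64.8) × √(1 − 0.25) = 0.176 × 0.866 = 0.15 SD.

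**Would MAR imputation remove this bias?** Not by itself. Imputing from arm and baseline places the missing scores on the line fitted to the observed ones, so the expected contrast is the same as with available cases. It can do better only through extra information, such as an observed 6-month score or predictors of dropout. For the rest, an explicit departure from MAR has to be modelled.

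**Time points side by side.** The check sorts participants by "response variables at the final measurement (6 months"; the primary outcome is the change to 3 months. The two groups overlap, since a dyad lost before 3 months is usually missing at 6 months too. They differ by the dyads lost between the two visits.

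**The case against.** The strongest reply is that the faulty branch would seldom be used. No baseline difference suggests MCAR and a difference suggests MAR; both lead to multiple imputation, shown with and without imputed data. In practice the rule may end close to what is proposed here. That stands, and it lowers the seriousness. It does not rescue the rule: a branch that its inputs cannot reach can be entered only by judgement after the data are seen.

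Other replies also hold. The baseline comparison is not the only input, and the pattern analysis is not limited to 6 months. Available-case regression is not always weaker than imputation: with the baseline score in the model it is unbiased in case (b). For continuous secondary outcomes, the multilevel models already use all available repeated measures in a likelihood-based fit, so the concern bears mainly on the primary outcome.

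A reader might infer more than the text supports:

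- **That the intention-to-treat set is abandoned.** The article defines it so: "The intention-to-treat population will include all information from participants randomized to each treatment arm". Analysing available cases by allocated arm does not contradict that.
- **That outcomes will be imputed after death.** The section does not mention deaths.
- **That it is a fault not to rank the imputed and unimputed results.** A condensed article can leave this to the analysis plan.
- **That with so few lost the check will usually show no difference, whatever the mechanism.** The 97% in case (b) contradicts this.

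**Conclusion.** The point holds as a fault in stated text, not as an omission that an analysis plan might fill. The rule asks observed data to separate MAR from MNAR, which they cannot do. Its MNAR branch uses an analysis that is unbiased only if missingness depends on arm and baseline score. Its baseline comparison is set at the wrong visit for the primary outcome.

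The non-identifiability rests on no numerical assumption; the size of any bias does. At about 10% loss it ranges from none (equal loss and equal departure in both arms) through 0.05 SD (15% against 5%, δ = 0.5), a tenth of the planned effect and about a third of a standard error, to about 0.15 SD in case (c), roughly one standard error. With 10% anticipated attrition, this should be fixed before outcome data are examined, but it does not invalidate the trial.

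**What to change.** - Delete the step that infers the mechanism and switches the analysis.
- Fix in advance one MAR-based primary analysis of the 3-month CarerQol-7D for all randomised dyads: multiple imputation by arm using baseline, the 6-month score and predictors of dropout, or an equivalent likelihood-based model.
- Whatever the pattern of missingness, add an MNAR sensitivity analysis, either arm-specific delta adjustment over a range stated in advance or a tipping-point analysis. This is needed because MAR imputation alone does not correct MNAR bias.
- Keep the unimputed available-case regression as a sensitivity analysis.
- Describe missingness by arm at 3 months for the primary outcome, and at 6 months for 6-month outcomes. Use the baseline comparison to describe and to choose imputation predictors, not to select the method.

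The cost is a revised paragraph and a little more analysis work. No further data or participants are needed, and the sample size is unchanged.

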### Ethics

The study has been submitted for approval to the Human Research Ethics Committee of the University of Groningen, the Netherlands. It was concluded that no assessment was needed based on the relevant law concerning scientific research in humans. However, the study will be conducted in accordance with the ethical standards of the 1964 Declaration of Helsinki (and subsequent revisions) and written informed consent will be obtained from all participating caregivers, and if possible, from the people with dementia.

## Discussion

More at Home with Dementia (*Beter Thuis met Dementie*) is a caregiver training program that we have adapted from a successful residential care setting in Australia and that will be delivered at a holiday location in the Netherlands. The presented study aims to determine the effectiveness of this intervention, primarily for the caregiver’s quality of life, after adapting it to the peculiarities of the Dutch health care system and to delivery in informal relaxed settings. This contrasts significantly with the approach used in the Australian studies where the intervention was delivered in nursing home or hospital settings. Standardized measures will be used to assess health-related primary and secondary outcomes among both the caregivers and the people with dementia. Additionally, we will use the opportunity to obtain qualitative outcome data from caregivers through focus groups. Ultimately, if the study outcomes confirm the intervention’s effectiveness, we anticipate that the results can be used to inform the implementation of this training program in routine care pathways. Using both the quantitative and qualitative results, we will also explore the generic aspects of the intervention that are not specific to dementia. For example, it is conceivable that the training content may apply to other conditions, such as Parkinson’s disease and multiple sclerosis, and for caregivers who do not live with the patient (e.g., children, other close relatives, or friends). Given the demographic changes in society, the growing burden of dementia, and the importance of care at home, we contend that intervention strategies should target not only the patient but also the informal caregiver. Therefore, this study will be of importance to both science and wider society.

## Abbreviations

ADL: Activities of Daily Living
CarerQol-7D: Care-Related Quality of Life-7 dimensions
CES-D: Center of Epidemiologic Studies-Depression
CMAI-C: Cohen-Mansfield Agitation Inventory-Community
DQI: Dementia Quality of Life Instrument
DSM: Diagnostic and Statistical Manual of Mental Disorders
EQ-5D + C: EuroQol-5 Dimensions + Cognition
GDS: Geriatric Deterioration Scale
GP: General Practitioner
HADS-A: Hospital Anxiety and Depression Scale, anxiety subscale
IADL: Instrumental Activities of Daily Living
M(C)AR: Missing completely at random
MAR: Missing at random
MNAR: Missing not at random
RAND-36/SF-36: RAND-36/short form 36
TOPICS-MDS: The Older Persons and Informal Caregivers Survey Minimum DataSet
VAS: Visual analog scale
